### Feasibility outcomes

Link to objectives 3, 4 and 5: evaluate the number of eligible patients within the recruiting site; evaluate the willingness of clinicians to recruit participants (the proportion of eligible patients who are offered participation in the study); evaluate the willingness of participants to be randomised (the proportion of eligible patients who agree to participate in the study).

As part of the trial processes, designated research associates will attend daily trauma meetings and fracture clinics held at the trial site. At these locations, they will identify potentially eligible patients who will be entered on a screening log. These logs will contain details of every patient who attends the trial site with an ankle fracture. The TMG will then monitor the number of screened patients who were eligible and offered participation for the trial and the number offered the trial who agree to participate.

Link to objective 7: to discuss the feasibility trial at a national consensus meeting to inform the design of a full RCT.

All the above outcomes will be discussed at a national consensus meeting to discuss more fully with patient, clinician and research representatives the feasibility of conducting a full RCT.

## Sample size

As this is a feasibility study, a formal power analysis for the sample size will not be undertaken, as the study is not designed to test a specific null hypothesis and infer significance to any observed treatment differences. Instead, we adopt a more informal approach, based on the aims of (i) assessing the distributional properties of the MOXFQ (specifically the variance) and (ii) assessing the likely participation rate (the proportion of eligible patients who are likely to agree to participate in the study). For the first aim, 50 participants in total, 25 in each arm, will be analysed. A sample size of 50 will allow us to estimate a participation rate of 75% to within a 95% confidence interval of ±12%. The data obtained from this study will inform the power analysis for the full study [11, 12].

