### Design

This is a single-centre feasibility randomised controlled trial. All patients with a fractured ankle under the care of an orthopaedic consultant in a single UK major trauma centre are potentially eligible. The trial will employ 1:1 random allocation, stratified by age and operative/non-operative management, implemented using a remote, independent telephone randomisation service. A total of 50 participants will be randomised.

All participants will follow a standardised protocol for both treatments. Baseline demographic data and pre-injury functional data using the MOXFQ and Olerud and Molander Ankle Score (OMAS) will be collected alongside the EuroQol EQ-5D-5 L health-related quality of life questionnaire.

A research associate will perform a clinical assessment and obtain X-rays in 6 weeks and 6 months to record any early and late complications. Functional outcome and health-related quality of life will be collected in 6 weeks, 3 and 6 months post randomisation.

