## Assignment of interventions

Pre-randomisation eligibility checks will be carried out to ensure that patients meet the eligibility criteria. Written informed consent for entry into the trial will be obtained prior to randomisation.

Allocation will be made using a secure, centralised computer-generated allocation sequence, using a telephone-based, independent randomisation service. A suitably qualified member of the research team will inform the treating clinical team of the allocated treatment.

Stratification on the basis of age will be used to discriminate between younger patients with normal bone quality sustaining high-energy fractures (under 50 years), and older patients (over 50 years) with low-energy (fragility) fractures related to osteoporosis [15, 16]. A second stratification, based on whether the patient receives surgery or not, will also be used. This will ensure that any effect related to severity of injury is equally distributed amongst the trial arms.

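### The ±12% precision for the participation rate takes 50 as the number of eligible patients, but 50 is the number randomised; the precision to expect is about ±10 points

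*Protocol article*

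**What the plan says.** The Sample size section rests the number of patients on two aims: the variance of the MOXFQ and the participation rate. It defines the rate as "the proportion of eligible patients who are likely to agree to participate in the study".

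For the variance aim it says: "For the first aim, 50 participants in total, 25 in each arm, will be analysed". For the participation aim it says: "A sample size of 50 will allow us to estimate a participation rate of 75% to within a 95% confidence interval of ±12" per cent.

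The Design section fixes what the 50 is: "A total of 50 participants will be randomised". Assignment of interventions gives the order of events: "Written informed consent for entry into the trial will be obtained prior to randomisation".

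The count of eligible patients comes from elsewhere. Under Feasibility outcomes, screening logs are kept, and "These logs will contain details of every patient who attends the trial site with an ankle fracture". From these the trial management group follows "the number of screened patients who were eligible and offered participation for the trial and the number offered the trial who agree to participate". The article gives no planned number of eligible or approached patients.

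**The concern.** A participation rate needs a denominator of people who could have said yes or no. The 50 randomised patients have all said yes, so they cannot be that denominator. They are the numerator, and the denominator is the larger number of eligible patients found while the 50 were being recruited. The precision sentence nevertheless uses 50 as if it were the denominator.

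The participation rate is one of only two aims used to set the size of the trial, and this half-width is the only numerical precision offered for either. The Recruitment section says the study will inform the recruitment rate of the main trial. The precision expected of that rate should therefore match the design.

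**Working it through.** **Inputs**
- Randomised: 50 (Design); analysed: 50, 25 per arm (Sample size).
- Rate: number agreeing divided by number eligible (Sample size, Objectives, Feasibility outcomes).
- Assumed rate p = 0.75, 95% confidence, stated half-width 12% (Sample size).
- Consent precedes randomisation (Assignment of interventions), so the 50 randomised are patients who agreed.

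**Step 1: reproduce the stated figure.** The usual large-sample half-width for a proportion is 1.96 × √(p(1 − p)/n). With p = 0.75 and n = 50:

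1.96 × √(0.75 × 0.25/50) = 0.120, or ±12.0 points.

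Solving for n at a half-width of 0.12 gives n = 50.02. The stated figure therefore uses 50 as the denominator. The calculation is correct for 50 eligible patients.

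**Step 2: put 50 where the design puts it.** If 50 is the number who agree and are randomised, the expected number of eligible patients at 75% is 50/0.75 = 66.7, about 67. Then:

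1.96 × √(0.75 × 0.25/66.7) = 0.104, or ±10.4 points.

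**Step 3: cross-check.** If recruitment stops at the 50th consenter, the numerator is fixed and the denominator is random. The half-width under that inverse sampling is 1.96 × p × √((1 − p)/50) = 1.96 × 0.75 × √(0.25/50) = 0.104, the same result. For 50 out of 67, the Wilson interval is 63.1% to 83.5% and the exact interval is 62.5% to 84.5%, half-widths of about 10.2 and 11.0 points.

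**Step 4: other rates.** With 50 consenters fixed:

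| Participation rate | Eligible patients (50/p) | 95% half-width, points |
|---|---|---|
| 30% | 167 | ±7.0 |
| 50% | 100 | ±9.8 |
| 60% | 83 | ±10.5 |
| 70% | 71 | ±10.6 |
| 75% | 67 | ±10.4 |
| 80% | 62.5 | ±9.9 |
| 90% | 56 | ±7.9 |

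The expression p√(1 − p) is largest at p = 2/3. There the half-width is 1.96 × 0.667 × √(0.333/50) = 0.107, so ±10.7 points is the ceiling.

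**Step 5: the other reading.** If 50 were the number of eligible patients, ±12 would stand, but only 50 × 0.75 = 37.5 patients, so 37 or 38, would be expected to be randomised. That contradicts the Design section.

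**The case against.** The strongest reply is that nothing is lost. The arithmetic is right for a denominator of 50, the section calls its approach informal, and the trial would deliver better precision than it promises. The 50 is also given separately for the variance aim, so correcting ±12 to about ±10 would not alter it. All of this stands, and it is why the point is minor. It does not make the sentence right: the half-width belongs to a different number of patients from the one the plan recruits. Nor is this a detail lost in condensing a longer protocol, because the article states a figure that disagrees with its own definition and design.

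A reader might infer two stronger things, and the article supports neither.

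- *That the two aims cannot both rest on 50 randomised patients.* They can. Randomising 50 gives the 25 per arm wanted for the variance, and more than the stated precision for the rate. A conflict would arise only if recruitment stopped at 50 eligible patients, and the Design section rules that out.
- *That the rate will be reported on the wrong denominator.* The rate is defined over eligible patients in Objectives, Feasibility outcomes and Sample size. The logs cover all ankle fracture attenders, and Participants requires a count of those unwilling to take part. The data for the right denominator will be there.

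**Conclusion.** The point holds as a minor correction. The ±12% treats 50 as the eligible patients, whereas 50 is the number who consented and were randomised. At a 75% rate the design implies about 67 eligible patients and a 95% half-width of about ±10.4 points, some 1.6 points narrower than stated. The error is conservative: by the same large-sample formula, no participation rate with 50 consenters gives more than about ±10.7 points. The sample size is not undermined.

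Two assumptions lie behind the 67: everyone who agrees is randomised, and every eligible patient is counted, including any who were not offered the trial. If some who agree are not randomised, more eligible patients are needed at the same rate and the interval narrows slightly. Agreement among those offered, which the trial management group also follows, has a different denominator and is a different quantity whenever some eligible patients are not approached.

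**What to change.** Replace the precision sentence in Sample size with wording such as: *Recruitment will continue until 50 participants are randomised. If 75% of eligible patients agree, and all who agree are randomised, this implies about 67 eligible patients and a 95% confidence interval of about ±10 percentage points. The denominator is all eligible patients on the screening log up to the 50th randomisation. Agreement among those offered the trial will be reported separately.*

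Reporting the two proportions separately keeps the willingness of clinicians to offer the trial apart from the willingness of patients to accept it.

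The cost is a few lines of text in one section. No change is needed to recruitment, data collection, the analysis or the number of patients.

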## Recruitment

Potentially eligible participants will be identified by the patients clinical care team in the emergency department, fracture clinics and trauma wards. The trauma team will undertake the initial approach, explaining that a study of ankle fracture rehabilitation is being conducted. If the patient is willing to be approached, a suitably qualified person will then provide verbal and written information about the study.

This feasibility study will specifically inform the recruitment rate for the main trial. However, recruitment has been estimated on audit data at the lead centre [13] and previous research in a related area completed at Warwick Clinical Trials Unit [14]. In the lead centre audit, 176 ankle fractures presented for an ankle pathway over a 16-month period, approximately 11 per month.

## Assignment of interventions

Pre-randomisation eligibility checks will be carried out to ensure that patients meet the eligibility criteria. Written informed consent for entry into the trial will be obtained prior to randomisation.

Allocation will be made using a secure, centralised computer-generated allocation sequence, using a telephone-based, independent randomisation service. A suitably qualified member of the research team will inform the treating clinical team of the allocated treatment.

Stratification on the basis of age will be used to discriminate between younger patients with normal bone quality sustaining high-energy fractures (under 50 years), and older patients (over 50 years) with low-energy (fragility) fractures related to osteoporosis [15, 16]. A second stratification, based on whether the patient receives surgery or not, will also be used. This will ensure that any effect related to severity of injury is equally distributed amongst the trial arms.

## Blinding

As the type of rehabilitation used is clearly visible, the participants cannot be blinded to their treatment. In addition, the treating surgeons cannot be blinded to the treatment but will take no part in the assessment of patients.

The questionnaire data will be collected and entered onto the trial central database via postal mechanisms by a research assistant/data clerk in the trial central office. All X-ray data will be reviewed by two independent assessors. The independent assessors will have no part in study procedures and will therefore be blinded to treatment allocation.

## Data

### Collection, management and monitoring

All electronic identifiable information will be held on a secure, password-protected database accessible only to essential personnel. Paper forms with identifiable information will be held in secure, locked filing cabinets within a restricted area. Personal data collected during the trial will be handled and stored in accordance with the 1998 Data Protection Act. Participants will be identified by a code number only. Direct access to source data/documents will be required for trial-related monitoring by authorised personnel only. All paper and electronic data will be retained for at least 10 years after completion of the trial.

The trial coordinator and data clerk will check and enter the data onto the trial database, which will be developed by the Programming Team at Warwick Clinical Trials Unit. Promotion of data quality will be achieved through implementation of a data management plan held at the Warwick Clinical Trials Unit.

### Analysis

Members of the trial management group, University of Warwick, University of Oxford and University Hospitals Coventry and Warwickshire NHS Trust, will have access to the final trial dataset. Given the small sample size, it is unlikely that formal hypothesis testing will be useful or informative. This data will be analysed using the software package STATA and will be presented using standard methods for statistical summaries of discrete and continuous data sets.

All data will be analysed and reported in accordance with the CONSORT statement. Baseline data will be summarised to check comparability between treatment arms and to highlight any characteristic differences between those individuals in the study, those ineligible and those eligible but withholding consent. As this is a feasibility study, the analysis will be performed through descriptive statistics rather than formal hypothesis testing. Results will be pooled and summarised using standard methods as appropriate and presented graphically to aid interpretation. Standard statistical summaries and graphical plots showing correlations will be presented for the primary outcome measure (MOXFQ) and all secondary outcome measures.

An exploratory linear regression analysis will also be undertaken in order to explore treatment group effects, after adjusting for the effects of patient age, fixation/non-operative management and gender.

Temporal patterns of any complications will be presented graphically, and if appropriate, a time-to-event analysis (Kaplan-Meier survival analysis) will be used to assess the overall risk and risk within individual classes of important complications (e.g. infection). The decision about whether to undertake a time-to-event analysis will be data-dependent, that is it will be dependent on the number of complications reported by study participants.

It seems likely that some data may not be available due to voluntary withdrawal of participants, lack of completion of individual data items or general loss to follow-up. Where possible, the reasons for data ‘missingness’ will be ascertained and reported. Although missing data is not expected to be a problem for this study, the nature and pattern of the missingness will be carefully considered—including in particular whether data can be treated as missing completely at random or missing at random. Reasons for ineligibility, non-compliance, withdrawal or other protocol violations will be stated and any patterns summarised. More formal analysis, for example using logistic regression with ‘protocol violation’ as a response is unlikely to be useful given the small sample size but may be considered if appropriate to aid interpretation.

Statistical methods for calculating the definitive RCT sample size will follow the conventional approach using four parameters: type I error, power, assumptions in the control group (response rate and standard deviation) and expected treatment effect.

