## Outcomes

### Patient-centred outcomes

Baseline data will be collected by the research associates from all participants and will include age, sex, general medical history and pre-injury functional and health status. This will be followed by ascertaining the current function and health status of the patient.

Link to objectives 1 and 6: evaluate the distributional properties of the MOXFQ in order to estimate the likely sample size required for a full RCT. Refine the statistical analysis plan to provide the most efficient and sensitive analysis.

The primary functional status outcome measure for this study is the MOXFQ. Other commonly used foot and ankle scores include the Olerud Molander Ankle Score (OMAS) and American Orthopaedic Foot and Ankle Score (AOFAS); however, they lack a methodologically robust approach in their development, in contrast to the MOXFQ. The MOXFQ is a validated questionnaire which is self-reported (filled in by the patient). It contains 16 items, each with five response options comprising three separate underlying dimensions: walking/standing problems (seven items), foot pain (five items) and issues related to social interaction (four items). Item responses are each scored from 0 to 4, with 4 representing the most severe state. The scale scores representing each dimension are produced by summing the responses to each item within that dimension. Raw scale scores are then converted to a metric (0–100; 100 = most severe) [7]. This will be collected to allow the distributional properties to be evaluated for a later sample size calculation.

Link to objective 2: evaluate the follow up and response rates to questionnaires

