The secondary objective measures proposed for the full RCT are health-related quality of life outcome measure for this study is the EQ-5D-5 L. The EQ-5D-5 L is a validated, generic health-related quality of life measure consisting of five dimensions each with a five-level answer possibility. Each combination of answers can be converted into a health utility score. It has good test-retest reliability, is simple for patients to use and gives a single preference-based index value for health status that can be used for broader cost-effectiveness comparative purposes [8]. Although cost-effectiveness analysis is not being carried out as part of this study, it is planned to be included in the definitive study. The methods will adhere to the recommendations of the NICE reference case, which included collection of EQ-5D-5 L. A record of all complications will also be included. The team will evaluate the proportion of these questionnaires that are completed and returned.

Radiographic evaluation of routine pre- and post-injury X-rays (taken at baseline, 6 weeks and 6 months after the injury) will also be collected from the trial team. Standard measurements of joint congruence, fracture angulation, fibular shortening and subluxation will be assessed [9]. We will again evaluate the proportion of these returned.

Whilst the exact number of appointments varies, most patients will be kept under review for 6 months as part of normal practise. The trial procedures will therefore mirror usual care with collection of all outcome measures at baseline, 6 weeks and 6 months face to face by a research associate in the follow-up fracture clinic. This will be alongside postal follow up in 3 months post injury. We will use techniques common in long-term cohort studies to ensure minimum loss to follow-up, such as collection of multiple contact addresses and telephone numbers, mobile telephone numbers and email addresses [10]. Refer to Table 1 for participant timeline.

**Table 1 Tab1:** Schedule of enrolment, interventions and assessments

	Enrolment	Allocation	Post-allocation		
Timepoint			6 weeks (±2 weeks)	3 months (±1 month)	6 months (±1 month)
Enrolment					
Eligibility screen	X				
Informed consent	X				
Allocation		X			
Interventions					
Functional brace		X	X		
Plaster cast		X	X		
Assessments					
Demographic data	X				
EQ5D-5 L/MOXFQ/OMAS	X		X	X	X
Complications			X	X	X
Exercise diary			X		
Physiotherapy input			X	X	X
Radiographs		X	X		X

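### The exploratory treatment model does not name the pre-injury score of the outcome as a covariate, and the definitive-trial sample size inputs have no place for what that score could contribute (minor)

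*Protocol article*

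**What the plan says.** The Analysis section of the protocol article states: "An exploratory linear regression analysis will also be undertaken in order to explore treatment group effects", and gives the adjusters in the same sentence: "after adjusting for the effects of patient age, fixation/non-operative management and gender". Two of the three correspond to the stratification factors under Assignment of interventions. No baseline or pre-injury score is named. The main analysis is otherwise descriptive.

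The score will be available. The Design section says: "Baseline demographic data and pre-injury functional data using the MOXFQ and Olerud and Molander Ankle Score (OMAS) will be collected". Patient-centred outcomes says: "Baseline data will be collected by the research associates from all participants and will include age, sex, general medical history and pre-injury functional and health" (that is, how the patient was before the injury). Current function and health are recorded next. Table 1 marks "EQ5D-5 L/MOXFQ/OMAS" at enrolment and at all three follow-up times.

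The sixth objective, repeated under Patient-centred outcomes and tied there to the MOXFQ, is: "Refine the statistical analysis plan to provide the most efficient and sensitive analysis".

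The Analysis section ends with the inputs to the definitive sample size: type I error, power, control-group assumptions (response rate and SD) and the expected treatment effect. A baseline-outcome correlation and a residual SD after baseline adjustment are not among them.

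**The concern.** For a continuous patient-reported outcome, whether to adjust for its earlier value is one of the first efficiency questions a definitive trial has to settle. This feasibility trial collects the score and has an objective about efficiency, yet the model it describes does not use the score. Nor does the sample size recipe provide a way for the answer to reach the definitive design.

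Two things are at stake, both modest. In this trial, with 25 per arm, the exploratory contrast may be less precise than it could be. It also carries any chance imbalance in pre-injury function, in proportion to how strongly that function predicts the outcome. For the definitive trial, the team may reach the design stage without a reported estimate of how much baseline adjustment would save.

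**Working it through.** **Inputs from the protocol article.** Sample size: "50 participants in total, 25 in each arm, will be analysed" (Sample size section). Named adjusters: three (Analysis section). The document gives no correlation, SD or target difference for the MOXFQ, so those are assumptions shown as a range.

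**The plan's own figure.** The only calculated figure is the precision for a 75% participation rate with 50 people: 1.96 × √(0.75 × 0.25 / 50) = 1.96 × 0.0612 = 0.120, or ±12 percentage points. It reproduces, and it does not depend on the regression covariates.

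**Degrees of freedom.** Intercept, treatment and three covariates use 5 parameters, leaving 50 − 5 = 45 residual df. One more covariate leaves 44.

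**Effect on the exploratory interval.** Let ρ be the partial correlation of the pre-injury score with the outcome, given the three named adjusters. Adding the score multiplies the residual variance by 1 − ρ². Estimating one more coefficient costs a factor of about (47/43)/(47/44) = 44/43 = 1.023 in variance. This is the expected inflation (N − 3)/(N − 3 − k) for k = 4 against k = 3; it treats covariates as normal, so it is approximate here. The t quantile moves from 45 to 44 df. The ratio of CI widths is therefore √[(1 − ρ²) × 44/43] × t(0.975; 44)/t(0.975; 45).

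**Effect on a definitive trial, for illustration.** With an assumed standardised difference of 0.3, 90% power and two-sided 5%, the unadjusted size is 2 × (1.960 + 1.282)² / 0.3² ≈ 234 per arm. Baseline adjustment multiplies this by 1 − ρ².

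| Assumed ρ | 1 − ρ² | CI width ratio, N = 50 | Definitive trial, n per arm |
|---|---|---|---|
| 0 | 1.00 | 1.012 | 234 |
| 0.1 | 0.99 | 1.007 | 232 |
| 0.2 | 0.96 | 0.992 | 225 |
| 0.3 | 0.91 | 0.966 | 213 |
| 0.4 | 0.84 | 0.928 | 197 |
| 0.5 | 0.75 | 0.877 | 176 |
| 0.6 | 0.64 | 0.810 | 150 |

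The covariate breaks even in this trial at ρ of about 0.15; below that the interval is very slightly wider.

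**How well the correlation can be learned.** By Fisher's z, with standard error 1/√(n − 3), an observed 0.3 in 50 people has a 95% CI of tanh(0.310 ± 1.96/√47), which is 0.02 to 0.53. An observed 0.5 has 0.26 to 0.68. If only 40 had both scores (an assumption), an observed 0.3 would have −0.01 to 0.56.

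**The case against.** The case on the other side is substantial. The model is exploratory, the study tests no hypothesis, and the adjusters it names are a principled choice: both stratification factors plus gender. The omission affects neither the number recruited nor the ±12 points. The pre-injury score is a recalled state that precedes a new injury. In previously healthy people it may bunch at the no-problem end and predict little, and part of what it predicts may already be carried by age, operative management and gender. Sizing the definitive trial on the unadjusted SD is accepted practice and errs on the safe side. All of this stands, and it is why the point is minor.

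A reader might infer more than the document supports, in three ways:

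- **That the planning parameter is lost.** It is not. The MOXFQ is recorded at enrolment and at every follow-up, so the correlation and the adjusted residual SD can be computed from the final dataset. The Analysis section also plans plots showing correlations, without naming the pairs of variables. What is missing is a stated intention to report these quantities and use them.
- **That a baseline-adjusted model is ruled out.** The article describes one exploratory model and excludes no others, and refining the analysis is itself an objective.
- **That the treatment contrast is biased.** Randomisation protects it. Chance imbalance affects a single estimate only so far as the score predicts the outcome, and baseline comparability is to be summarised anyway.

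What the objection does not remove is that the article chose to name the covariates and the sample size inputs, and on both lists it passed over a score already in hand that bears directly on its own efficiency objective. An exploratory model in a feasibility trial is a natural place to try it, and a correlation near zero would itself be useful to know.

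**Conclusion.** The point holds as a minor one. The stated covariate list omits the pre-injury score of the outcome, and the stated inputs for the definitive sample size omit the baseline-outcome correlation and the adjusted residual SD.

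The size of the gain rests entirely on an assumed partial correlation. At N = 50 it runs from an interval about 1% wider at 0, through 3% narrower at 0.3, to 12% narrower at 0.5. The possible loss is trivial and the possible gain is moderate. The stake is larger for the definitive trial, where the same correlations of 0.3 and 0.5 would take an illustrative 234 per arm to 213 and 176. Those totals also assume a standardised difference of 0.3 and 90% power, neither of which comes from the document.

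**What to change.** 1. In the Analysis section, add the pre-injury score of the same outcome as a continuous covariate beside age, operative management and gender, for the MOXFQ and likewise for the OMAS and EQ-5D-5L.
2. Say which score is meant. Both pre-injury and current status are recorded at baseline, and the MOXFQ is described as three dimension scores. The covariate should be the pre-injury score, not the current post-injury one, on the same dimension or summary score as the outcome being analysed.
3. Report the baseline-outcome correlation with a 95% CI, and the residual SD with and without baseline adjustment.
4. Add these to the listed inputs for the definitive sample size, and keep the unadjusted SD as the conservative sizing case, because the correlation will be only loosely estimated.

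**Cost.** A few words of analysis text and one degree of freedom (45 to 44), with no new data. The covariate is recalled and may sit at the floor, so the report should show its distribution before anyone leans on the adjusted figures.
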